## Abstract

**Background:**

Acupuncture has demonstrated beneficial effects on sleep outcomes in patients with chronic insomnia disorder (CID); however, robust evidence from randomized controlled trials evaluating its efficacy as an adjunctive intervention to facilitate discontinuation of non-benzodiazepines (NBZDs) remains limited.

**Objective:**

To evaluate the clinical efficacy and safety of electroacupuncture as an adjunctive therapy for reducing NBZDs use in patients with chronic insomnia disorder.

**Methods:**

This single-blind, randomized, controlled trial will enroll 78 adults with chronic insomnia disorder (ICSD-3TR) who have used NBZDs for >6 months. Participants will be assigned 1:1 to electroacupuncture or sham electroacupuncture. Both groups will undergo a standardized, gradual NBZDs tapering protocol over 6 weeks and receive standardized sleep hygiene education. Participants in the electroacupuncture group will receive electroacupuncture treatment three times per week at predefined acupoints (Baihui, Sishencong, Anmian, Shenting, Yintang, Hegu, Taichong, Neiguan, Shenmen, Sanyinjiao, Shenmai, and Zhaohai), whereas participants in the control group will receive non-penetrative sham electroacupuncture. The primary outcome is the successful discontinuation rate of NBZDs at the end of the 6-week treatment period. Secondary outcome measures included subjective sleep scales, objective sleep parameters (polysomnography and actigraphy), and daytime functioning assessments, among others. Safety will be assessed through systematic monitoring and documentation of adverse events. Statistical analyses will follow the intention-to-treat principle using mixed-effects models.

**Conclusion:**

This trial aims to provide high-quality evidence regarding the efficacy and safety of electroacupuncture as an adjunctive intervention for NBZDs tapering in patients with chronic insomnia. The findings may support the integration of a low-risk, non-pharmacological treatment option into clinical practice and address an important gap in current insomnia management strategies.

**Clinical trial registration:**

https://itmctr.ccebtcm.org.cn/mgt/project/view/1998715224785551360, ITMCTR2025002446.

## Introduction

Chronic insomnia disorder (CID) is characterized by persistent difficulties in initiating or maintaining sleep, occurring at least three times per week for a duration of no less than 3 months, and accompanied by clinically significant daytime impairment (1). With an estimated prevalence of 25.0% among Chinese adults (2), CID represents the most prevalent sleep disorder in China. It is commonly associated with fatigue, cognitive impairment, emotional dysregulation, and depressive symptoms, leading to substantial impairments in quality of life and functional capacity (3). Pharmacological therapy remains a cornerstone of CID management, with approximately one-fifth of patients relying on sedative–hypnotic medications to initiate or maintain sleep (4). Benzodiazepine receptor agonists (BZRAs), including both benzodiazepines (BZDs) and non-benzodiazepines (NBZDs), are the most frequently prescribed agents. These medications exert their hypnotic effects primarily by enhancing gamma-aminobutyric acid (GABA)–mediated inhibitory neurotransmission, resulting in central nervous system suppression and subsequent sedative and anxiolytic effects (5).

However, long-term BZRAs use is associated with tolerance development and a range of adverse outcomes, including daytime somnolence, cognitive impairment (6), increased risk of falls (7), motor vehicle accidents (8), and elevated all-cause mortality (9). In response to growing concerns regarding dependence and misuse, the U.S. Food and Drug Administration mandated updated boxed warnings in 2020 highlighting the risks of physical dependence, withdrawal reactions, abuse, and addiction associated with BZRAs use (10). Despite these warnings, patient awareness of the dependence potential and withdrawal risks of BZRAs remains limited, contributing to a low spontaneous discontinuation rate of approximately 6% (11).

Various strategies have been explored to facilitate safe and effective BZRAs discontinuation. Pharmacological substitution approaches, although commonly employed, may provoke adverse effects such as panic symptoms (12), increase fall risk (13, 14), or anticholinergic side effects including dry mouth and dysgeusia (15). Moreover, individualized and standardized protocols for BZRAs dose conversion and tapering remain inadequately established (16). In the absence of medications specifically approved by the U.S. Food and Drug Administration or the China National Medical Products Administration for BZRAs dependence or withdrawal, non-pharmacological approaches have attracted increasing attention. Acupuncture has been incorporated into the most recent Chinese clinical guidelines for the diagnosis and treatment of insomnia as a recommended therapeutic option (17, 18). As a widely utilized complementary therapy for insomnia, acupuncture has demonstrated efficacy in improving total sleep time, sleep efficiency, and both subjective and objective sleep quality, while also alleviating cognitive impairment and mood disturbances, with a favorable safety profile (19, 20).

More recently, interest has emerged in the potential role of acupuncture as an adjunctive intervention during BZRAs tapering. A randomized controlled trial by Yeung et al. found no significant difference between electroacupuncture and sham acupuncture in discontinuation rates or withdrawal symptom severity during a four-week tapering protocol (21). Subsequent methodological analyses suggested that the inclusion of both BZDs and NBZDs within the same cohort may have confounded the findings, as different BZRAs subtypes are associated with distinct pharmacokinetic profiles and withdrawal trajectories (22).

NBZDs, such as zolpidem, zopiclone, and zaleplon, are currently recommended as first-line pharmacological treatments for insomnia in many clinical guidelines owing to their shorter elimination half-lives, lower residual sedation, and comparatively reduced dependence potential relative to traditional BZDs (23). Accordingly, NBZDs have become the most commonly prescribed hypnotics in China. Notably, a recent clinical trial reported that electroacupuncture significantly alleviated withdrawal symptoms, improved sleep architecture, increased deep sleep duration, and reduced medication dependence in patients with chronic insomnia undergoing zolpidem tapering (24). The divergent findings of existing studies suggest that acupuncture may exert differential effects during NBZDs discontinuation specifically, rather than across all BZRAs subtypes.

Taken together, current evidence regarding acupuncture as an adjunctive therapy for hypnotic tapering remains limited and inconsistent, particularly with respect to NBZDs. Therefore, this single-blind, randomized, sham-controlled trial is designed to evaluate the efficacy and safety of electroacupuncture as an adjunctive intervention for NBZDs tapering in patients with chronic insomnia disorder. By systematically assessing medication discontinuation rates, sleep quality, daytime functioning, and withdrawal-related outcomes, this study aims to provide robust evidence to inform clinical decision-making in the management of long-term hypnotic use.

## Methods

### Study design

This study is a single-center, randomized, controlled, single-blind clinical trial conducted at the Department of Acupuncture and Moxibustion, Zhejiang Provincial Hospital of Traditional Chinese Medicine. The trial period is scheduled from September 2025 to December 2026. Eligible participants will be randomly assigned in a 1:1 ratio to either the electroacupuncture group or the sham electroacupuncture group using a centralized randomization system.

A total of 78 participants will be enrolled, with 39 participants allocated to each group. Each participant will undergo three study phases: a screening period, a 6-week treatment period, and a follow-up period, with an overall study duration of approximately 12–13 weeks (Figure 1). The study protocol has been approved by the Ethics Committee of Zhejiang Provincial Hospital of Traditional Chinese Medicine (Approval No.: 2025-KLS-532-01) and will be conducted in accordance with the Consolidated Standards of Reporting Trials (CONSORT) guidelines and the Standards for Reporting Interventions in Clinical Trials of Acupuncture (STRICTA). The study flowchart and procedure are depicted in Figure 1 and Table 1.

**Figure 1 fig1:**
[figure not shown]
Flow diagram. ACT, actigraphy; AES, Acupuncture Expectancy Scale; BHWSS, Benzodiazepine Hypnotics Withdrawal Symptom Scale; CSD, Consensus Sleep Diary; ESS, Epworth Sleepiness Scale; FSS, Fatigue Severity Scale; GAD-7, Generalized Anxiety Disorder 7-item; ISI, Insomnia Severity Index; NBZDs, Non-Benzodiazepines; PHQ-9, Patient Health Questionaire-9; PSG, polysomnography; PSQI, Pittsburgh Sleep Quality Index; VAS, Visual Analogue Scale; 5-HT: 5-hydroxytryptamine.

**Table 1 tab1:** Trial processes chart.

Week	0	1	2	3	4	5	6	7	8	9	10
	Baseline	Treatment phase						Follow-up phase			
Patients											
Enrolment	**×**										
Sign informed consent	**×**										
General information	**×**										
Medication diary	**×**	**×**	**×**	**×**	**×**	**×**	**×**	**×**	**×**	**×**	**×**
PSG	**×**						**×**				
ACT	**×**						**×**				
Groups											
Acupuncture group		18 treatments									
Sham- acupuncture group		18 treatments									
Outcome measurement											
Successful drug discontinuation rate							**×**				
CSD	**×**		**×**		**×**		**×**		**×**		**×**
ISI	**×**		**×**		**×**		**×**		**×**		**×**
PSQI	**×**						**×**				**×**
ESS	**×**						**×**				**×**
FSS	**×**						**×**				**×**
GAD-7	**×**						**×**				**×**
PHQ-9	**×**						**×**				**×**
NBZDs reduction rate	**×**		**×**		**×**		**×**		**×**		**×**
BHWSS			**×**		**×**		**×**		**×**		**×**
VAS	**×**		**×**		**×**		**×**		**×**		**×**
AES	**×**										
Blinding assessment		**×**		**×**			**×**				
Adverse events											
Reasons for dropouts or withdrawals	**×**	**×**	**×**	**×**	**×**	**×**	**×**	**×**	**×**	**×**	**×**

ACT, actigraphy; AES, Acupuncture Expectancy Scale; BHWSS, Benzodiazepine Hypnotics Withdrawal Symptom Scale; CSD, Consensus Sleep Diary; ESS, Epworth Sleepiness Scale; FSS, Fatigue Severity Scale; GAD-7, Generalized Anxiety Disorder 7-item; ISI, Insomnia Severity Index; NBZDs, non-benzodiazepines; PHQ-9, Patient Health Questionaire-9; PSG, polysomnography; PSQI, Pittsburgh Sleep Quality Index; VAS, Visual Analogue Scale; 5-HT, 5-hydroxytryptamine.

### Participants

Participants will be recruited primarily from patients with chronic insomnia disorder who attend the Department of Acupuncture and Moxibustion at Zhejiang Provincial Hospital of Traditional Chinese Medicine and who report long-term use of NBZDs.

The diagnosis of chronic insomnia disorder will be established according to the International Classification of Sleep Disorders, Third Edition, Text Revision (ICSD-3TR), published by the American Academy of Sleep Medicine in 2023 (1).

### Inclusion criteria

Participants must meet all of the following criteria:

(1) Aged 18–65 years, regardless of sex;(2) Meeting the diagnostic criteria for chronic insomnia according to ICSD-3TR;(3) Participants were required to have insomnia symptoms of mild to moderate severity (Insomnia Severity Index ≤ 21) while taking NBZDs (25);(4) Continuous use of NBZDs for chronic insomnia for more than 6 months, with medication adherence exceeding 50% of the treatment period and a dosing frequency of at least three nights per week during the 2 weeks prior to screening;(5) Use of NBZDs recommended in the Chinese Guideline for the Diagnosis and Treatment of Insomnia in Adults (2023 edition), with each dose not exceeding the guideline-recommended maximum (18);(6) Self-reported history of at least one unsuccessful attempt to discontinue NBZDs independently;(7) A clear willingness to reduce NBZDs dosage;(8) No history of acupuncture or other needle-based therapies within the past 6 months;(9) Ability and willingness to comply with the study protocol and provision of written informed consent.

### Exclusion criteria

Participants meeting any of the following criteria will be excluded:

(1) Polysomnography (PSG) findings indicating an apnea-hypopnea index ≥15 events/h, a periodic limb movement index with arousal ≥15 events/h, rapid eye movement (REM) sleep without atonia, or evidence of dream enactment behavior (26).(2) Engagement in shift work within 2 weeks prior to screening or during the study period, or planned travel across more than two time zones.(3) Use of anxiolytics, antidepressants, antipsychotics, melatonin, or melatonin receptor agonists within 2 weeks prior to screening or during the study period.(4) History of alcohol or substance use disorder within the past year.(5) History of severe psychiatric disorders (e.g., bipolar disorder or major depressive disorder).(6) Severe cardiovascular, hepatic, renal, hematological, or respiratory disease, or uncontrolled infectious disease.(7) Aversion to acupuncture, needle phobia, or inability to receive acupuncture due to infection, inflammation, scarring, or trauma at or near the selected acupoints.(8) Pregnancy or breastfeeding.(9) Participation in another interventional clinical trial within the past 6 months.

### Withdrawal criteria

Participants will be withdrawn from the study if any of the following occur:

(1) Participants who develop intolerable severe withdrawal symptoms during the NBZDs tapering process.(2) Voluntary withdrawal at the participant’s request.(3) Withdrawal of informed consent.(4) Emergence of exclusion criteria during the study period.(5) Poor treatment compliance, defined as attendance at fewer than 50% of scheduled acupuncture sessions.(6) Occurrence of adverse events that preclude continued participation or pose a risk to participant safety.

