### NBZDs tapering protocol

Based on the 2025 European clinical practice guideline recommending a gradual dose reduction of 10–25% per week for NBZDs (27), and supported by two clinical studies that successfully employed a weekly 25% reduction strategy (21, 28), NBZDs will be reduced at a rate of 25% of the baseline dose per week. If participants experience intolerable withdrawal symptoms during tapering—such as exacerbation of insomnia, anxiety, or agitation—the dose will be temporarily reverted to the previous level. Tapering will be reattempted during the subsequent evaluation cycle (1 week per cycle).

Throughout the treatment period, participants will attend weekly in-person consultations and receive twice-weekly telephone follow-ups. Dose adjustments will be conducted through a shared decision-making process, enabling participants to actively engage in symptom monitoring and self-management under physician supervision. Final dosage modifications will require investigator approval.

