### Outcome measures

#### Primary outcome measures

The successful discontinuation rate at the end of the 6-week treatment was defined as the proportion of patients who had completely ceased NBZDs use (any dose) during the final week of treatment (days 36–42). Medication adherence was verified using patients’ daily diaries and medication records. Patients completed a daily diary card, on which they recorded the date, medication name, dose, time of administration, and any adverse reactions. The diary cards were returned to the physician at each weekly visit, and prescription records were cross-checked by an independent observer every 3 weeks. Any discrepancy between the diary and medication records will be resolved by consensus of two blinded independent investigators based on all available data (daily diaries, medication records). Urine or blood drug concentration testing was not performed to confirm participants’ self-report of hypnotic discontinuation, due to the short half-life of NBZDs (requiring daily sampling, which is logistically infeasible) and the increased participant burden that would likely raise dropout rates. The multi-source adjudication approach described above was considered a reliable alternative.

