### Efficacy evaluation criteria

① Primary Efficacy Outcome Measures

The primary efficacy outcome is the successful discontinuation rate of NBZDs at the end of the 6-week treatment period. Between-group differences in discontinuation rate will be evaluated using regression-based methods appropriate for binary outcomes.

② Secondary Efficacy Outcome Measures

a. Subjective Sleep Efficacy Evaluation

Subjective sleep outcomes, including the Insomnia Severity Index (ISI) and Pittsburgh Sleep Quality Index (PSQI), will be analyzed using longitudinal mixed-effects models incorporating repeated measurements across predefined study time points to estimate treatment effects over time.

b. Objective Sleep Efficacy Assessment

Objective sleep parameters derived from PSG and ACT will be analyzed using longitudinal mixed-effects models to account for within-subject correlation and to evaluate changes across study time points.

c. Daytime Functioning Assessment

Daytime functioning outcomes will be analyzed using longitudinal mixed-effects models to assess treatment effects across time.

d. NBZDs Reduction Response Evaluation

Medication reduction responses, including NBZDs reduction rate, withdrawal symptoms, and craving scores, will be evaluated using regression-based models appropriate to outcome type, with longitudinal modeling applied where repeated measurements are available.

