### Sample size

The expected discontinuation efficacy rate for the sham acupuncture group in the sample size calculation was derived from a randomized controlled trial that enrolled 144 long-term benzodiazepine users (21). However, this trial yielded a negative result, which might be attributable to the simultaneous inclusion of both BZDs and NBZDs in the study medication (22). Therefore, only the sham acupuncture group discontinuation rate of 10.83% was adopted from that trial, while the expected successful discontinuation rate for the acupuncture group was based on our pilot study.

A pilot study was conducted at our center prior to the main trial to assess the feasibility of the intervention and to obtain preliminary estimates of effect size. Ten eligible patients with chronic insomnia disorder who had used NBZDs regularly for >6 months received electroacupuncture (three times per week for 6 weeks) combined with the standardized 6-week NBZD tapering protocol (25% dose reduction every week). The successful discontinuation rate was 50.00% (5/10). No serious adverse events were reported. Detailed pilot study results are provided in Supplementary Appendix S2.

Based on expected outcomes and relevant published literature (21), this study hypothesized that after treatment, the discontinuation efficacy rates of NBZDs at 6-week post-treatment for the electroacupuncture group and sham needle and sham electroacupuncture group would be 50.00 and 10.83%, respectively. This study set *α* = 0.05 and 1-*β* = 0.90, employing a two-sided test with equal sample sizes between treatment and control groups. Referencing the sample size estimation formula for comparing efficacy rates between two groups from Sun Zhenqiu’s Medical Statistics, the calculation formula was as follows:

$$n=1641.4/{\left[\frac{\left(u_{\alpha }+u_{\beta }\right)}{\sin^{-1}\sqrt{P_{1}}-\sin^{-1}\sqrt{P_{2}}}\right]}^{2}$$

where 
$u_{\alpha }$
=1.96 (for 
α
=0.05, two-sided), 
$u_{\beta }$
=1.282 (for 
β
=0.10), P_1_ = 50.00%, and P_2_ = 10.83%. The calculation yields n = 31.7 ≈ 32 cases. Accounting for dropout rates, the clinically set dropout rate is 20%, resulting in a final sample size of 39 participants per group, totaling 78 participants across both groups.

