### Data management

Data collection will encompass three aspects: (1) Participants independently completing relevant scale assessments in the acupuncture treatment room. The assessment requires approximately half an hour. During this period, participants may consult dedicated assessment physicians regarding any questions. (2) Participants will complete sleep diaries at home throughout the study period under physician guidance.

This study will train data outcome assessors to enhance participant compliance, collect high-quality complete datasets, and facilitate follow-up completion. Dedicated personnel will perform data entry, receiving specialized training in data input procedures, coding protocols, and secure storage practices. Data analysts in this study will receive training in data evaluation and analysis methodologies. This study strictly safeguards participant privacy through the following primary measures: ① Requiring participants to provide only research-related personal information during the study process; ② Store data on designated computers with restricted access, ensuring the specific folders containing data are password-protected; ③ Only personnel involved in the research can access participants’ personal information, and this information will be destroyed upon completion of the study.

The full analysis set (FAS) will include all randomized participants who receive at least one treatment session and have at least one post-baseline assessment, consistent with the intention-to-treat principle. Missing outcome data will be handled using likelihood-based estimation within mixed-effects models under the missing-at-random assumption. Multiple imputation will be conducted as a sensitivity analysis. The safety set (SS) will include all participants who receive at least one treatment session. The pilot data and the main trial data will be pooled after completion of the main trial to conduct sensitivity analyses assessing the robustness of the conclusions.

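### Participants withdrawn because the taper was intolerable would probably have no days 36–42 outcome, and no stated rule counts them as not discontinued

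*Protocol article*

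**What the plan says.** All references are to the protocol article.

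- **Withdrawal criteria.** The list opens "Participants will be withdrawn from the study if any of the following occur", and item (1) is "Participants who develop intolerable severe withdrawal symptoms during the NBZDs tapering process". Voluntary withdrawal and withdrawal of consent are separate items, so item (1) is imposed by the protocol and is not the participant's choice.
- **NBZDs tapering protocol.** For intolerable symptoms short of that, "the dose will be temporarily reverted to the previous level", and the reduction is tried again one week later.
- **Primary outcome measures.** Success is the proportion who "had completely ceased NBZDs use (any dose) during the final week of treatment (days 36–42"). Diaries and medication records verify it, and "Any discrepancy between the diary and medication records will be resolved by consensus of two blinded independent investigators".
- **Efficacy evaluation criteria.** "Between-group differences in discontinuation rate will be evaluated using regression-based methods appropriate for binary outcomes".
- **Data management.** "The full analysis set (FAS) will include all randomized participants who receive at least one treatment session and have at least one post-baseline assessment". Missing outcomes are handled by likelihood within mixed-effects models under missing at random, with multiple imputation as a sensitivity analysis.
- **Statistical analysis.** The missing-data rule is repeated, and the mixed models are linear and tied to longitudinal outcomes.
- **Table 1.** The discontinuation outcome is marked at week 6 only. The medication diary and the reasons for dropout are marked at every week to week 10.

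**The concern.** Withdrawal under item (1) is close to being the failure event itself. A participant who cannot tolerate the taper is unlikely to be free of NBZDs on days 36–42. Removing that person from the study before the window turns a probable failure into a missing value. A similar participant who is kept in by dose reversion and still takes a dose in that week is an observed failure. The line between symptoms that lead to reversion and symptoms that lead to withdrawal is not defined.

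The stated missing-data rule does not repair this. Missingness caused by taper failure is informative about the outcome, so missing at random is a poor assumption unless earlier doses and symptoms enter the model.

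Two things are at stake. The reported discontinuation rates would be too high in any arm with such withdrawals. The comparison could also be biased: more withdrawal under sham works against electroacupuncture, and more under electroacupuncture works for it. Equal withdrawal gives no bias when there is no true effect, but it enlarges the difference when there is one.

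**Working it through.** **Does any stated rule settle these cases?**

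- Adjudication resolves conflicts between diary and records. It does not supply absent data.
- The full analysis set keeps these participants if they have one post-baseline assessment, but gives no score for their primary outcome.
- The mixed-model rule covers the primary outcome only loosely. A single week-6 binary value analysed by regression has no repeated measures of its own from which likelihood could recover information, so without auxiliary data the analysis reduces to observed cases.

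That data would stop at withdrawal is an inference from the wording that participants leave the study. The article does not say so outright.

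**Inputs.** From Sample size: 50.00% vs 10.83%, 39 per group, and "the clinically set dropout rate is 20"%. The planned difference is 50.00 − 10.83 = 39.17 points. The article gives no withdrawal share for item (1). The shares q below are assumptions, none above the planned 20% dropout, and every withdrawn participant is taken as a true failure.

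**Formula.** Let p be the true rate with withdrawn participants counted as failures. The observed-case rate is then p/(1 − q).

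| q, electroacupuncture / sham | Electroacupuncture | Sham | Difference (planned 39.2) |
|---|---|---|---|
| 5% / 5% | 0.50/0.95 = 52.6% | 0.1083/0.95 = 11.4% | 41.2 |
| 10% / 10% | 0.50/0.90 = 55.6% | 0.1083/0.90 = 12.0% | 43.5 |
| 20% / 20% | 0.50/0.80 = 62.5% | 0.1083/0.80 = 13.5% | 49.0 |
| 5% / 15% | 52.6% | 0.1083/0.85 = 12.7% | 39.9 |
| 15% / 5% | 0.50/0.85 = 58.8% | 11.4% | 47.4 |

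Of 39 participants, 5% is about 2 and 10% about 4.

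**Scale.** The sampling SD of the planned difference is √(0.5 × 0.5/39 + 0.1083 × 0.8917/39) = 0.094, or 9.4 points. The shifts at equal 5% and 10% are 2.1 and 4.4 points (0.4123 − 0.3917 and 0.4352 − 0.3917 before rounding), under half an SD.

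**No true effect.** Take 25% in both arms, an assumption. At 15% / 5% the bias is 0.25/0.85 − 0.25/0.95 = 0.294 − 0.263 = +3.1 points. At 5% / 15% it is −3.1 points, and at equal shares it is zero. Simulated rejection at two-sided 0.05 (39 per arm, pooled two-proportion z-test, 100,000 trials, observed cases):

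| q, electroacupuncture / sham | Rejects for electroacupuncture | Rejects for sham |
|---|---|---|
| 10% / 10% | 2.6% | 2.6% |
| 5% / 15% | 1.2% | 5.0% |
| 15% / 5% | 4.9% | 1.3% |

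With withdrawn participants scored as failures, each direction stays at 2.5–2.7%.

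**Imputation that uses earlier diary doses.** Suppose this gives the withdrawn half their arm's success rate (assumed). The rate becomes p + q × p/2 = p(1 + q/2), and the difference 39.17 × (1 + q/2). At equal 5%, 10% and 20% that is 40.1, 41.1 and 43.1 points. Imputation reduces the problem but does not remove it.

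**The case against.** The strongest reply is that this is an omission. The document is a journal article, and scoring of missing binary outcomes and follow-up after withdrawal are commonly left to a full protocol or analysis plan. If the missing-at-random rule does not clearly reach the primary outcome, the article is merely silent. If it does reach it, observed cases is not literally the analysis stated. Prescription records, cross-checked every three weeks, may also survive withdrawal. And under intention to treat, someone not shown to have stopped could naturally stay out of the numerator.

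Part of this stands. The loss of data is inferred, the coverage of the primary outcome is loose, and the observed-case figures illustrate what the rule amounts to; they do not reproduce a specified analysis. But the article does fix two things: taper failure leads out of the study, and missing outcomes are treated as missing at random. Neither suits this endpoint, and the intention-to-treat reading is nowhere written down.

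The second reply is size. Dose reversion, weekly visits and twice-weekly calls should leave few item (1) cases, and 25% steps can reach zero in about four of the six weeks. If electroacupuncture eases withdrawal, as the trial expects, sham withdrawals should be the more frequent, and 5% / 15% gives 39.9 points against 39.2. The 49.0-point figure requires every planned dropout to be a taper failure, although five other withdrawal reasons are listed. All of this stands and limits the expected effect. It does not remove the bias, and the direction of any imbalance cannot be assumed in advance.

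**Conclusion.** The concern holds. As written, the protocol withdraws probable failures from the study because the taper failed, probably loses their primary value, and offers only a missing-at-random rule that does not fit that reason for loss. Stated discontinuation rates would be too high. With a true effect and equal withdrawal of 5–10% per arm, the difference would be overstated by about 2 to 4 points. With no true effect, a 10-percentage-point imbalance in withdrawal moves the difference by about 3 points in either direction and roughly doubles false rejection on the favoured side, from about 2.6% to about 5%.

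These sizes rest on assumed withdrawal shares, on all withdrawn participants being true failures, and on no data being collected after withdrawal. The likely effect is modest, but it falls on the primary endpoint and is cheap to prevent. It should be fixed; confidence is medium.

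**What to change.** 1. Reword withdrawal criterion (1) so that it stops the taper or the sessions, with the participant remaining in the study.
2. For those who consent, continue the medication diary to day 42 and week 10. Table 1 already schedules it that far.
3. State that, in the primary analysis, participants stopped for withdrawal symptoms who have no days 36–42 data are scored as not discontinued. The reasons for withdrawal that Table 1 records every week identify them.
4. Keep multiple imputation as the sensitivity analysis, with earlier diary doses in the imputation model.

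The cost is protocol wording, a few extra diary weeks for participants who stop early, and slightly lower stated discontinuation rates. The scoring rule should be set before unblinding. The diary change is worth making promptly, because days not recorded may not be recoverable.
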